### 3.6 MANAGING ADVERSE / UNEXPECTED OUTCOMES

*Describe what measures you have in place in the event that participants experience adverse effects arising from their involvement in the project (e.g. adverse drug reaction, revelation of illegal activity, or unexpected distress due to questioning)*

Despite the intervention, some participants may develop major depression or become acutely suicidal. To manage this risk, participants will be encouraged throughout the project to seek help from a professional if they feel they are getting worse. To facilitate this, a section of the website will provide information on seeking professional help for each country involved. Participants will also receive feedback from their survey results on their level of symptoms, and encouraged to seek professional help if their symptom levels indicate major depression. Currently many people with depression do not seek and/or receive help for their symptoms. The links provided on the website will channel potential participants using the Internet for mental health information to appropriate sources of help. Participants will be informed they can discontinue participation at any time.

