Participants will be recruited to the project website (<http://www.moodmemos.com>) by advertising on Google, links from depression and mental health websites and blogs, and posts on mental health forums. See Appendix A for a letter proforma asking whether webmasters would like to put a link to the moodmemos.com website on their website. An online screening questionnaire (Patient Health Questionnaire-PHQ9; Kroenke & Spitzer, 2002) will assess level of depressive symptoms and probable diagnosis of major depressive disorder. Participants who have sub-threshold depression symptoms will be provided with a plain language statement and invited to participate. They will be asked to complete a number of online questionnaires assessing psychological distress (K10; Kessler et al., 2002), functioning (Work and Social Adjustment Scale; Mundt et al., 2002) unpleasant experiences that may have caused depression (List of Threatening Experiences; Brugha et al., 1985), coping strategies, knowledge about depression, and sociodemographics (see Appendix B for all questionnaires), and to provide a name and email address. Those who meet admission criteria will be randomised to receive the active intervention or a control of educational information about depression. The intervention will be run on the internet and will be automated as much as possible through php computer scripts. The active group will receive email messages based on strategies thought to be effective and feasible by depression experts (Morgan & Jorm, 2009). See Appendix C for the text of each active message and an example of the layout of the email.

The control group will receive email messages based on information about depressive disorders, such as prevalence and risk factors. See Appendix D for the text of each control message and an example of the layout. The intervention will run for 6 weeks with emails sent twice a week. In addition to baseline, assessments will take place midway through the intervention, at the end of the intervention and 6 months after the end of the intervention. Total time commitment is estimated to be no more than 3 hours, including time to read each email as well as time taken to complete the four assessments.

Continuous outcomes (e.g. depressive symptoms) will be evaluated using mixed effects regression models, and dichotomous outcomes (e.g. presence of a depressive disorder) will be evaluated using logistic regression expressed as odds ratios with their 95% confidence intervals.

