## 3.2 POTENTIAL RISKS TO PARTICIPANTS

*Identify, as far as possible, all potential risks to participants (e.g. physical, psychological, social, legal or economic etc.), associated with the project and the setting (e.g. overseas) in which the project is conducted. It may be useful to consider the study profile above and your response to participant details in section 2*

Minimal discomfort is anticipated for participants. The intervention will not be an imposition on participants, as they will be seeking assistance for their symptoms. There is a small chance that completing the questionnaires may cause distress, however, a systematic review of the evidence on whether participation in psychiatric research causes distress concluded that a minority of participants become distressed, but there is no evidence of long-term harm. Positive reactions are more common than negative ones (Jorm et al., 2007). Furthermore, questionnaires that screen for depression are already commonly used on the internet, for example on beyondblue's website.

There is also a risk that some participants will experience worse mental health despite the intervention (see 3.6 for management of this risk). There is a risk that some participants may attempt suicide, although we believe this is a small risk as research indicates that those with sub-threshold depression are less likely to report suicidal symptoms than those with major depression (Karlsson et al., 2007).

Karlsson, L., et al., Differences in the clinical characteristics of adolescent depressive disorders. *Depression and Anxiety*, 2007. 24(6): p. 421-432.

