### 3.3 MANAGING POTENTIAL RISKS

*Describe what measures you have in place to minimize these potential risks to participants and to ensure that support is available if needed.* [Depending on risks, participants may need additional support (e.g. external counseling) during or after the study]

Some potential participants may screen positive for major depression. The screening questionnaire is a brief self-report measure that cannot give a diagnosis on its own, but can indicate whether a diagnosis is probable. In this instance, participation in the project may not be the most appropriate strategy to improving mental health. These participants will not be eligible for participation; rather, they will be informed that they may have major depression and should seek appropriate professional help. Appropriate sources of help will be provided on the website (see Appendix F).

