We will continue to advertise the study and recruit participants in the same manner as before (primarily through Google advertising). We will aim for a sample size of 1600 participants in this second phase of the study. This is based on a power analysis indicating that a sample of 393 per condition would give 80% power to detect a small effect size (0.2 standard deviations between conditions) on a continuous outcome measure assuming a correlation of 0.5 between pre- and post-test scores. As approximately 50% of participants in phase one did not complete the post-test assessment, a total sample of 1600 allows for a similar rate of attrition. 1600 participants is a feasible target given that 1336 participants with sub-threshold depression were recruited in phase one.

To clarify, the inclusion criteria will now be:

- a. 18 years or older
- b. Access to the internet at least once per week
- c. Resident of Australia, New Zealand, Canada, Ireland, United Kingdom, USA
- d. Any score on the PHQ-9 depression questionnaire
- e. Informed consent

2) The second change we propose is to send an additional reminder email requesting the participant to complete post- and follow-up assessments, bringing the number of reminders to two. This is because up to 50% of participants did not complete assessments, and the reminder email resulted in about 25% more responses. Therefore, a second reminder may lead to a significantly higher response rate.

3) The third change we propose is to amend the wording of the help-seeking question asked at mid-point, post intervention and follow-up. This is so that we can collect more specific information about treatments received by participants. The question will be changed from:

"Have you visited a health professional (e.g. doctor, counsellor, psychologist) to help deal with your depression during the past [3 weeks] / [6 weeks] / [6 months]? (Yes/No)"

to:

"Which treatments for depression have you received from a professional during the past [3 weeks] / [6 weeks] / [6 months]? (multiple responses allowed)

• Nothing, just the consultation

• Psychological therapy

o Acceptance and commitment therapy

o Behaviour therapy

o Cognitive behaviour therapy

o Dialectical behaviour therapy

o Family therapy

o Mindfulness-based cognitive therapy

o Problem solving therapy

o Psychoanalytic psychotherapy

o Supportive psychotherapy or supportive counselling

o Not sure what type

• Medication

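### Section 3.6 names acute suicidality as a risk, but the visible text describes no suicide-specific response: the only answer-based prompts to seek help fire at the major-depression level.

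*Protocol*

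**What the plan says.** Protocol section 3.6 states the risk directly: "some participants may develop major depression or become acutely suicidal". It then lists its measures. Participants are encouraged throughout to seek professional help if they feel worse. The website gives help information for each country. Participants get feedback on their symptom level, and they are "encouraged to seek professional help if their symptom levels indicate major depression". They may stop at any time.

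Section 3.3 covers the entry screen. Of people who screen positive for major depression it says that "they will be informed that they may have major depression and should seek appropriate professional help".

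Section 3.2 accepts that a participant may attempt suicide but calls the risk small, because "those with sub-threshold depression are less likely to report suicidal symptoms than those with major depression".

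Section 1.3 says the intervention "will be automated as much as possible through php computer scripts". Besides baseline, "assessments will take place midway through the intervention, at the end of the intervention and 6 months after the end of the intervention".

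The Request for Amendment, section 4.1, opens phase two to people with "Any score on the PHQ-9 depression questionnaire". Its section 4.3 expects no new risks from the unchanged content and then names one, that the emails may be taken as a substitute for treatment. Section 4.4 answers this with a statement in the plain language statement and a footer in the emails, both recommending professional help.

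**The concern.** Section 3.6 names two outcomes, but the prompt it ties to a participant's answers is keyed to only one of them. Major depression and suicidal thinking overlap without being the same thing, and section 3.2 itself treats suicidal symptoms below the major-depression level as less common, not absent. Phase one enrolled only people below that level, so at entry the trigger sat above everyone in the trial.

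What is at stake is participant safety. The trial has no clinical contact, and the automated reply to a questionnaire is the one point at which the study can react to what a person has just reported. If that reply depends only on the overall symptom level, a suicidal thought reported at a lower level gets no targeted answer under the rule as written.

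A smaller issue follows from the amendment. The reason given in section 3.2 for a small suicide risk is that the sample is sub-threshold. Phase two removes that restriction, and the amendment does not return to the subject.

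**Working it through.** There is no figure of the plan's to reproduce. The check is to list every stated safety measure, ask what sets it off, and see whether any responds to suicidality.

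| Measure | Where | What sets it off | Stated response to suicidality |
|---|---|---|---|
| Notice to seek help at the entry screen | 3.3 | Own answers: screen positive for major depression | None |
| Prompt to seek help within feedback | 3.6 | Own answers: level indicating major depression | None |
| Feedback on symptom level | 3.6 | Own answers, no threshold | None stated; wording not shown |
| General encouragement to seek help | 3.6 | Participant's own sense of getting worse | None |
| Help pages by country | 3.6 (sources of help in Appendix F, per 3.3) | Nothing; always available | Content not shown |
| Freedom to stop | 3.6 | Participant's choice | None |
| Statement and email footer, phase two | Amendment 4.4 | Nothing; same for any score | None |

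**Step 1: count the triggers.** Three of the seven measures use a participant's answers. Two of those three carry a prompt to seek help, and both require results that indicate major depression. None is set off by a suicidal answer.

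**Step 2: follow one case.** Take a participant below the major-depression level who endorses a self-harm item. The 3.3 notice and the 3.6 prompt do not fire. Symptom-level feedback is given, but the only help-seeking advice attached to it in the text is the conditional clause. The general encouragement applies if the person feels worse, which a person with long-standing thoughts may not. The help pages and, in phase two, the footer are there whatever the answer was. So this person receives several messages, but none is stated to follow from the suicidal answer.

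**Step 3: check that the case can occur on the protocol's own terms.** Section 3.2 compares suicidal symptoms in sub-threshold and major depression and finds them less likely in the former. That leaves room for the case.

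**Step 4: count the occasions.** There is 1 baseline assessment and 3 later ones (midway, end, 6 months), so 1 + 3 = 4 assessments per participant. Section 3.6 does not say at which of these feedback is given, so 4 is an upper limit on the scheduled assessments at which a new rule could act. The phase-two footer would appear up to 6 weeks x 2 emails = 12 times where it is included. Amendment 4.4 promises it for the Mood Memo emails and does not say outright whether that covers the control emails.

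**Step 5: carry the 3.2 reason into phase two.** The reason is a comparison that favours sub-threshold people. Phase two admits any PHQ-9 score. For entrants with full-threshold depression the same comparison points the other way. Amendment sections 4.3 and 4.4 do not mention suicide.

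**The case against.** The strongest reply has four parts.

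- **Section 3.6 does address the named risk below threshold.** The general encouragement is offered as the way to manage both outcomes and has no score condition. In addition, symptom-level feedback goes to everyone. This stands. A reader might infer that people below the trigger receive nothing individual, and the protocol does not support that: the threshold governs only the advice to seek help, not the feedback.
- **The self-harm item is assumed.** No visible section says that any questionnaire asks about self-harm, and Appendix B is not shown. This also stands, so the case in Step 2 is conditional. It does not remove the fact that section 3.6 names acute suicidality and describes no specific response to it.
- **Material not shown may answer the point.** Appendix F and the plain language statements could contain crisis contacts or suicide wording. This stands for static contacts. They would help, but they would not change the trigger that sections 3.3 and 3.6 state.
- **Phase-two entrants with full depression are covered.** They meet the 3.6 trigger when their results indicate major depression, and the amendment adds a recommendation of professional help. This stands. A reader might infer that the amendment left this group without protection. It did not; what is out of date for them is the reasoning in section 3.2, and rewording it alone changes little in practice.

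The reply narrows the point. It does not supply a response tied to a suicidal answer, which is what the visible text lacks.

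**Conclusion.** The point holds in a limited form. The protocol names acute suicidality as a possible outcome and plans individual automated feedback, yet both stated answer-based prompts to seek professional help depend on results that indicate major depression. On the visible text, a self-harm answer below that level triggers no stated prompt.

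This rests on three assumptions: that the questionnaires include a self-harm item, that the item is asked again after entry if the rule is to act later, and that the feedback wording, which is not shown, adds nothing specific to suicide.

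The size cannot be given as a number of people at risk. A reader might take phase-one enrolment, or the phase-two target, as the measure. Those figures count people enrolled or planned, and the protocol gives no frequency of suicidal answers to apply to them.

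The 3.2 statement is a secondary point and is well supported: its reason does not fit a sample admitted at any PHQ-9 score. Neither part affects the trial's estimates or error rates. I would class this as a cheap safety improvement that the investigators should make.

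**What to change.** 1. In the automated feedback of section 3.6, add a condition: any positive response to a self-harm item brings advice to seek help and country-specific crisis links, whatever the total score. Apply it identically in both arms and at every assessment where the item is asked, including the entry screen. The clinical investigators should set the wording. If no questionnaire contains such an item, section 3.6 should say so and state how acute suicidality is to be handled.
2. State in section 3.6 at which assessments feedback is given.
3. For phase two, revise the suicide-risk statement in section 3.2 so that it describes a sample with any PHQ-9 score.

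The cost is one extra condition in a process that is already largely scripted, plus a few revised sentences. The downside is slightly more prompting to seek help. Because the rule is the same in both arms, that prompting is balanced by design.

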### 3.7 POTENTIAL RISKS TO RESEARCHERS

*Will there be any significant risks to researchers associated with the project and the setting (e.g. overseas) in which the project is conducted. (e.g. personal safety, health, emotional well being)?* [Refer to the University's [Environmental Health & Safety Manual](#) for more information]

☐ YES ☒ NO (If YES, how will such risks be addressed)

## 4. INFORMATION FOR PARTICIPANTS AND INFORMED CONSENT

Before research is undertaken, the informed and voluntary consent of participants (and other properly interested parties) is generally required (refer Section 2 of the National Statement for more details). Information needs to be provided to participants at their level of comprehension about the purpose, methods, demands, risks, inconveniences, discomforts and possible outcomes of the research. Such information is often provided in a written **Plain Language Statement**. Each

participant's consent needs to be clearly established (e.g. by using a signed **Consent Form**, returning an anonymous survey or recording an agreement for interview).

#### 4.1 PROVIDING INFORMATION FOR PARTICIPANTS

(a) Will you be providing participants with information in a written Plain Language Statement?

☒ YES ☐ NO (If NO, provide details of the protocol you will use to explain the research project to participants and invite their participation?)

(b) Will arrangements be made to ensure that participants who have difficulty understanding English can comprehend the information provided about the research project?

☐ YES ☒ NO (If YES, what arrangements have been made? If NO, give reasons.  
Only participants who have sufficient English skills will be eligible to participate.

#### 4.2 PLAIN LANGUAGE STATEMENT (IF APPLICABLE)

##### CONFIRM THAT THE PLAIN LANGUAGE STATEMENT WILL:

|                                                                                                                                                                                                                                         | YES                                 | NOT APPLICABLE                      |
|-----------------------------------------------------------------------------------------------------------------------------------------------------------------------------------------------------------------------------------------|-------------------------------------|-------------------------------------|
| 1. be printed on University of Melbourne letterhead                                                                                                                                                                                     |  |                                     |
| 2. include clear identification of the University, the Department(s) involved, the project title, the Principal and Other Researchers (including contact details), and the study level if it is a student research project.             |  |                                     |
| 3. provide details of the purpose of the research project                                                                                                                                                                               |  |                                     |
| 4. provide details of what involvement in the project will require (e.g., involvement in interviews, completion of questionnaire, audio/video-taping of events), and estimated time commitment                                          |  |                                     |
| 5. provide details of any risks involved and the procedures in place to minimise these.                                                                                                                                                 |  |             |
| 6. advise that the project has received clearance by the HREC                                                                                                                                                                           |  |                                     |
| 7. (if the sample size is small), confirm that this may have implications for protecting the identity of the participants                                                                                                               |             |  |
| 8. include a clear statement that if participants are in a dependent relationship with any of the researchers that involvement in the project will not affect ongoing assessment/grades/management or treatment of health (if relevant) |             |  |
| 9. state that involvement in the project is voluntary and that participants are free to withdraw consent at any time, and to withdraw any unprocessed data previously supplied                                                          |  |                                     |
| 10. provide advice as to arrangements to be made to protect confidentiality of data, including that confidentiality of information provided is subject to legal limitations (see ** below)                                              |  |                                     |
| 11. provide advice as to whether or not data is to be destroyed after a minimum period (if relevant)                                                                                                                                    |  |             |
| 12. provide in the footer, the project HREC number, date and version of the PLS                                                                                                                                                         |  |                                     |
| 13. provide advice that if participants have any concerns about the conduct of this research project that they can contact the Executive Officer, Human Research Ethics, The University of Melbourne, ph: [name]; [contact]      |  |                                     |

[\*\*Re 10 – it is possible for data to be subject to subpoena, freedom of information request or mandated reporting by some professions. Depending on the research proposal you may need to specifically state these limitations]

